## Abstract

**Background:** Opportunistic prostate-specific antigen (PSA) screening may reduce prostate cancer mortality risk but is associated with false positive results, biopsy complications and overdiagnosis. Although different organisations have emphasised the importance of shared decision making (SDM) to assist men in deciding whether to undergo prostate cancer screening, recent evaluations show that the available decision aids fail to facilitate SDM, mainly because they do not consider the patients’ perspective in their design. We aim to systematically develop and test a patient decision aid to promote SDM in prostate cancer screening, following the Knowledge to Action framework. **Methods:** (1) Feasibility study: a quantitative survey evaluating the population and clinician (urologists and general practitioners) knowledge of the benefits and risks derived from PSA determination and the awareness of the available recommendations. Focus groups to explore the challenges patients and clinicians face when discussing prostate cancer screening, the relevance of a decision aid and how best to integrate it into practice. (2) Patient decision aid development: Based on this data, an evidence-based multicomponent SDM patient decision aid will be developed. (3) User-testing: an assessment of the prototype of the initial patient decision aid through a user-testing design based on mix-methods (questionnaire and semi-structured review). The decision aid will be refined through several iterative cycles of feedback and redesign. (4) Validation: an evaluation of the patient decision aid through a cluster-randomised controlled trial. **Discussion:** The designed patient decision aid will provide balanced information on screening benefits and risks and should help patients to consider their personal preferences and to take a more active role in decision making. **Conclusions:** The well-designed patient decision aid (PDA) will provide balanced information on screening benefits and risks and help patients consider their personal preferences.

## 1. Background

Shared decision making (SDM) has been defined as the key to successful patient-centred care [1], and consequently, researchers, clinicians, patients and health policy representatives have made a considerable effort to implement SDM in clinical practice [2]. Current clinical practice guidelines for the early detection of prostate cancer recommend for clinical decision making a personalised prostate-specific antigen (PSA)-based management to improve the risk–benefit ratio of the screening strategy. Some important critical issues regarding the PSA determination (i.e., the poor harmonisation of the assays) in the clinical framework are, however, still neglected in the current guidelines, and a major focus of recommendations on those aspects would be needed to improve their effectiveness [3,4]. In addition, evidence suggests that clinicians have traditionally underestimated the adverse impact of PSA [5], and consequently, it is rarely explained to patients [6], although several studies show that most patients would like to be informed [7]. According to previous data, fewer than 30% of men discuss PSA screening with their clinicians, and these dialogues do not promote SDM [8], although it is critical to assist men in making informed decisions in opportunistic screening.

The decision to undergo PSA testing for prostate cancer is a difficult one for men, and patient decision aids have been proposed to promote SDM. Patient decision aids (PDA) are tools that help patients learn about a condition and review the possible benefits, harms and scientific uncertainties about potential options. They are particularly useful when the efficacy and outcomes are unclear, as well as when the outcomes are clear but the trade-off between benefits and risks requires subjective judgment, as in PC screening, where most men overestimate the benefits of PC screening and are unaware of the limitations. These issues, as well as difficult concepts such as overdiagnosis and overtreatment, make decision aids especially useful in approaching the clinician–patient discussion in PC screening [9]. In 2010, the Spanish Ministry of Economy and Competitiveness evaluated PDAs for patients with PC to help them to decide on their treatment and management [10]. However, there are no evaluations in PDAs for PC screening.

Several randomised clinical trials have evaluated PDAs for PC screening, mainly among primary care patients, with contradictory results. According to a recent meta-analysis [11], the available PDAs face both design and implementation challenges, and although they improve men’s knowledge regarding PSA benefits and risks, they fail to promote SDM. Hence, how to design and implement PDAs in PC screening represents a large gap in the existing literature. The meta-analysis identified the lack of consideration of the patients’ perspective as the main concern in the design and implementation of these previous PDAs, resulting in a poor analysis of the best strategy to help patients to evaluate which benefits and harms are most important to them. There are many factors that may determine whether men receive screening, including their personal preferences and factors related to their clinician. Recent research has highlighted that men do not have uniform reactions to PC screening information: some prefer an active approach and want to receive PSA screening after being informed, while others prefer not to receive it [12]. There are also some PC screening determinants which can influence the patient’s decision such as education, age and prior PSA testing, but these factors have not been adequately addressed in previous decision-aids. Some studies have proposed the use of a well-calibrated risk prediction model to define PSA thresholds for identifying or excluding advanced PC as an aid to personalise the management of the diagnostic workup. The proposed PSA thresholds, being associated with the related predictive values, may allow for an individualised approach to the diagnostic workup, assisting patients in making an informed decision [13].

Barriers also exist at multiple levels in the healthcare system [14]. Some clinicians do not agree with the information included in the tools. The pressure to see a larger volume of patients in a shorter period of time [15] is also a known barrier, together with a lack of experience in SDM [16]. However, previous PDAs did not consider the patients and clinicians’ characteristics, preferences and attitudes. In addition, patients should receive information contextualised to their particular setting in order to help them in their informed decision. Information regarding test properties, such as the likelihood of having a false- positive result or overdiagnosis, are not frequently explained to patients [17]. Moreover, most of the available data derives from clinical trials with high-risk populations, which differ quite significantly from the unselected population undergoing opportunistic screening in clinical practice. Our group has previously evaluated those factors associated with the presence of false-positive and -negative results in PSA determinations carried out in clinical practice through the inclusion of 572 men with a negative PSA result and 1081 mean with a positive result from 20 primary health centres in the Valencian Community who have been followed up for 2 years [18]. The information of this previous study about the probability of having a false positive result will provide patients with information applicable to their setting.

Therefore, this study seeks to overcome the fact that available PDAs have shown no effect on screening discussion, patient’s decision satisfaction or actual screening. The main result will be a PDA that will not only provide patients with information but will also specifically target the promotion of SDM. This PDA will be evaluated through a trial to mimic the conditions in primary care, where the distribution of a decision aid has been recommended.

The overall aim of this project is to systematically develop and test a PDA to promote SDM in PC screening, following the Knowledge to Action (KTA) framework [19].

## 2. Materials and Methods

This study will be guided by the KTA framework [19] to develop, test and validate a PDA to promote SDM in PC screening. The KTA framework is adequate for this study because it includes the integration of different sources of evidence together with researchers and knowledge-users to improve the decision process in PC screening and to provide more effective health services.

### 2.1. Study Overview

The study detailed in this protocol paper consists of four phases: feasibility testing (Phase 1); PDA development (Phase 2); usability testing (Phase 3); and evaluation in a cluster random controlled trial study (Phase 4) (Figure 1).

#### 2.1.1. Phase 1: Feasibility Test

In this phase, we will assess the feasibility of the PDA. First, we will evaluate the knowledge among the target population and clinicians (urologists and general practitioners) about the benefits and risks of opportunistic screening for PC and the available recommendations through a quantitative survey. Second, through focus groups, we will explore the challenges men and clinicians face when addressing the benefit and risk of PC screening, including the core information both groups need to establish an informed discussion. We will also analyse the patients’ and clinicians’ attitudes, reactions and preferences regarding different formats of a PDA and establish the preferential criteria for its implementation in practice.

##### Participants

Knowledge surveys

For the population’ s knowledge evaluation, we will survey the population belonging to the Valencian Community, Spain (according to the Spanish National Statistics Institute, in 2021, there were 1,389,725 men > 40 years). We will include men > 40 years old living in the Valencian Community, and men who have a PC diagnosis will be excluded. We estimate that, for a precision of 5% with a 95% Confidence Interval (CI), at least 1067 men would be required on a conservative estimate that 50% of the men could be unaware of the PSA benefits and risks. This precision will allow for analysis by subgroups. The sampling will be conducted by geographic area (the three provinces of the Valencian Community) and population habitat (rural and urban) and will be stratified by age (40–50; 50–70; >70).

For the clinician (urologist and general practitioners) knowledge surveys, we will select clinicians through their respective scientific societies. According to a previous survey [20], 56.1% of the general practitioners and 64.3% of the urologists discussed the impact of PSA on mortality with patient; for a precision of 5% (95% CI), 369 general practitioners and 345 urologists will be surveyed after being randomly selected from the list obtained from scientific societies.

2.Focus groups with users

To explore clinicians’ perceptions, we will include a purposive sample of urologists and general practitioners working in two Health Departments in the Valencian Community (Health Department Alicante-General Hospital, 255,439 habitants; and Health Department Alicante-S. Joan d’Alacant, 233,115 habitants).

To explore patients’ perceptions, eligible patients (men > 40 years who do not have a PC diagnosis and are willing to participate in focus groups, with a varied profile of age and educational level) will first be identified by the general practitioners working in the two Health Departments in the Valencian Community. The clinicians will ask them for their permission to be contacted by a member of the research team, who will then offer them to participate in the study.

At least three focus groups of patients and clinicians (8–12 participants in each group) will be made to triangulate the information and obtain cross-validity. We will also carry out one focus groups with 8–12 participants each belonging to the Prostate Cancer Association (ANCAP) in Spain in order to compare the outcomes with those who do not have a PC diagnosis.

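### The population survey's stated precision (5%) and its stated size (1067 men) do not belong together: 5% needs 385 men, and 1067 is the size for 3%

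*Protocol article*

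**What the plan says.** Under section 2.1.1 (Phase 1: Feasibility Test), Participants, the protocol article plans a telephone survey of men over 40 in the Valencian Community and states that "for a precision of 5% with a 95% Confidence Interval (CI), at least 1067 men would be required". The assumed proportion is given as "on a conservative estimate that 50% of the men could be unaware of the PSA benefits and risks". The population is given too: "in 2021, there were 1,389,725 men > 40 years".

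The next sentence draws a conclusion from the precision: "This precision will allow for analysis by subgroups". The sampling factors follow: three provinces, rural or urban habitat, and three age bands. The text gives no target precision for any subgroup and no allocation of the sample across strata.

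**The concern.** All the inputs of a one-proportion precision calculation are printed (precision, confidence level, assumed proportion, population size), yet they do not lead to the printed sample size. This is not a detail left to a fuller document. A target and a size are presented as following from one another, and they do not.

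The subgroup sentence rests on the stated precision. A survey that only just achieves 5 points overall is a much weaker basis for subgroup estimates than one that achieves 3 points. A reader cannot tell which of the two the investigators planned, nor how precise a province or age-band estimate is meant to be. Section 2.4 says the surveys are only now being designed, so the text can still be settled before fieldwork.

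**Working it through.** **Inputs** (all from section 2.1.1, Participants): precision d = 0.05, read as the half-width of the interval; 95% confidence, so z = 1.95996 and z² = 3.84146; p = 0.50; N = 1,389,725; stated size 1067.

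**Formula:** n = z² p(1 − p) / d². With the finite population correction, n_c = n / (1 + (n − 1)/N). Here z² p(1 − p) = 3.84146 × 0.25 = 0.960365.

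**Where 1067 comes from (d = 0.03):**
- n = 0.960365 / 0.0009 = 1067.07
- n_c = 1067.07 / (1 + 1066.07/1,389,725) = 1066.25, which rounds up to exactly 1067

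**What the stated 5% gives (d = 0.05):**
- n = 0.960365 / 0.0025 = 384.15
- n_c = 384.15 / (1 + 383.15/1,389,725) = 384.04
- either way, 385 men

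The stated size is 1067 / 384.15 = 2.78 times what the stated precision needs.

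**Other readings that might rescue 5% with 1067:**

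| Reading | Men needed |
|---|---|
| 5% as the full interval width (d = 0.025) | 1537 (1535 with the finite population correction) |
| 99% interval, d = 0.05 | 664 |
| One-sided 95%, d = 0.05 | 271 |
| Continuity correction, d = 0.05 | 404 |
| ±5 points in each of 2 equal strata (2 × 385) | 770 |
| ±5 points in each of 3 equal strata (3 × 385) | 1155 |
| ±5 points in each of 6 equal strata (6 × 385) | 2310 |

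None gives 1067. A 99.9% interval at 5 points gives 1083, which is near, but the article states 95%. Going from 385 to 1067 would need a design effect of 2.78 or non-response of 1 − 385/1067 = 64%, and neither is mentioned.

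**The article's own convention.** The clinician surveys in the same section also use 5% and 95%. With p = 0.561 and 0.643 the formula gives 378.4 and 352.7, so 379 and 353, against 369 and 345 printed. These are within 3%, so 5% there is a half-width, as it is read here.

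**What each size gives** (half-width = z √(0.25/n), p = 0.5; equal split into thirds assumed):

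| Total | Overall | Per equal third |
|---|---|---|
| 385 | 0.98/√385 = ±5.0 points | 0.98/√128.3 = ±8.7 points |
| 1067 | 0.98/√1067 = ±3.0 points | 0.98/√355.7 = ±5.2 points |

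The allocation is not stated, so the equal split is an assumption. With 1067 men, a subgroup holding half the sample would have ±4.2 points (n = 533.5), and one holding a sixth would have ±7.3 points (n = 177.8).

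**The case against.** The strongest defence is that nothing is lost. 1067 matches 3 points so exactly that the likeliest explanation is a wrong digit in the precision, with the sample size as intended. If 5% was meant, 1067 more than meets it. Equal thirds of 1067 give ±5.2 points, so one-way subgroup analysis is workable whatever the label says. This is a descriptive Phase 1 survey, and the cluster-randomised trial in Phase 4 does not depend on it. All of that stands and limits the weight of the point. It does not remove the contradiction between the printed target and the printed size.

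A reader might infer more, and the article does not support it:

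- **That interviewing is inflated about 2.8-fold.** This follows only if 5 points overall was truly the aim. If 3 points was intended, no interview is surplus.
- **That the survey will report a wrong precision.** The Analysis subsection of 2.1.1 plans 95% confidence intervals for the item frequencies. Those come from the data and the achieved sample, not from the planning label.
- **That the subgroup claim fails in crossed cells.** Province, habitat and age are named as sampling and stratification factors. The article nowhere promises estimates for their combinations.
- **That the clinician surveys are also mis-sized.** For these the article says "369 general practitioners and 345 urologists will be surveyed after being randomly selected". Both sizes give ±5.06 points at the stated proportions, which is 5% at the precision quoted. Nor does the gap from 379 and 353 prove an undisclosed finite population: the plain formula also returns 369 and 345 at p = 0.60 and p = 0.66.

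**Conclusion.** The point holds, and it is minor. At 95% confidence and p = 50%, a precision of 5 points requires 385 men. The stated 1067 is the size for 3 points, and the article gives nothing that bridges the two. The subgroup sentence therefore refers to the wrong precision: the difference is between about ±8.7 and about ±5.2 points per equal third.

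This rests on reading precision as a half-width, which the clinician surveys support, and on simple random sampling, since no design effect is stated. The per-third figures also assume an equal split. The error is conservative for the stated target. It should not be read as showing that the survey is too small or that the randomised trial is affected.

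**What to change.** Reconcile the two figures in section 2.1.1, Participants, in one of two ways:

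1. Keep 1067 and restate the precision as ±3 points overall, adding that this gives about ±5 points (5.2) in each of three equal one-way strata, such as provinces or age bands. This is the natural choice if subgroup estimates are wanted.
2. If ±5 points overall is all that is wanted, restate the minimum as 385 and drop the subgroup sentence, because thirds of 385 give only about ±8.7 points.

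If 1067 in fact came from a design effect or a non-response allowance, state that basis instead.

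The first route costs one line of text and changes nothing in the conduct. The second would reduce the number of interviews by up to 1067 − 385 = 682, at the price of subgroup precision.

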##### Data Collection

Knowledge surveys

The general population will be surveyed by phone (through a Computer-assisted Telephone Interviewing -CATI- platform by the random selection of telephone numbers), indicating the purpose of the study and requesting oral informed consent. Clinicians will be contacted and invited to take part through their scientific societies, and we will survey them using a Google questionnaire. Both surveys will be developed after reviewing the available scientific literature and will be validated through the Delphi method with experts (urologists, general practitioners, epidemiologists and psychologists). The final surveys will be piloted before use, and adaptations will be made to improve their clarity.

2.Focus groups with users

Each focus group will be performed according to a previously established topic guide considering the following issues: discussion about the barriers and facilitators to promoting SDM and their relationship with the information patients need; aspects related to the patient’s role (passive or active) in screening decision making. In addition, several procedures for presenting the information, including different formats, will be presented to evaluate the patients and clinicians’ reactions and preferences, according to the Control Preferences Scale [21]. They will also be asked about the ideal setting and moment in the decision-making process to present the decision aid. A trained interviewer will conduct each focus group. All discussions will be audiotaped, and field notes will be kept.

##### Analysis

Knowledge surveys

The demographic data of the surveyed subjects will be coded. The frequency of response will be described in each of the items of the survey, expressed with 95% confidence intervals, and statistically significant differences in selected independent variables will be analysed using the Pearson χ^2^ test for categorical variables and the Mann–Whitney U test for continuous variables, (*p* < 0.05).

2.Focus groups with users

Two researchers will triangulate the information obtained from the different focus groups. First, a careful transcript reading will be carried out, and the text will be split up into meaningful information units. These units will be coded following a mixed strategy (emerging and predefined codes according to the study objectives), and categories will be developed based on grouping codes with the same theme. Finally, the points of agreement and disagreement will be analysed.

#### 2.1.2. Phase 2: Patient Decision Aid Development

Based on the findings from Phase 1 and a review of the available evidence, we will follow the standards of the International Patient Decision Aid Standards Collaboration [22] to develop the evidence-based multicomponent PDA. The International Patient Decision Aids Standards provide explicit guidance on content, the development process and effectiveness.

The PDA will include information about PSA application in the early detection of PC; available recommendations from the European Urologist Society [23]; well-balanced information about population-specific benefits and risks based on individual risk factors and the previous results in this setting [15]; and a discussion of the limitations of the results (false-positive and false-negative results, overdiagnosis). The initial PDA will be in the Spanish language; the patient-directed components will target a Grade 8 literacy level (readability score) [24]. The PDA will be designed in an iterative fashion by study team members, including a graphics designer and a computer programmer to include a combination of numbers, graphics and narratives.

#### 2.1.3. Phase 3: User-Testing

In this phase, we will assess the prototype of the initial PDA through a user-testing design based on mix-methods (a questionnaire and a semi-structured interview). The PDA will be refined through several iterative cycles of feedback and redesign.

##### Participants

As in Phase 1, men > 40 years of varied socio-demographic profiles (described in Phase 1) who do not have a PC diagnosis will be contacted by their general practitioners. We will also include patients from the ANCAP (contacted by the urologist president of the association) and a convenience sample of clinicians (urologists and general practitioners) not involved in the development process for content accuracy. Research has shown that up to 80% of usability issues can be identified through five to eight participants [25]. We anticipate conducting up to three usability cycles of four to five participant dyads in a process of iterative redesign.

